**Fig. 3 Fig3:**
[figure not shown]
Sampling of inflammatory cytokines from the stratum corneum by tape stripping

All participants will receive general skin-care advice to avoid soap and bubble bath, use mild cleansers and shampoos that have been specifically designed for babies, and avoid using baby wipes based on NICE guidance on infant skin care [51]. Treatment will be prescribed for babies with AD, as per standard protocols. Parental usage of products will be recorded with eczema treatment diaries. Contact will be maintained with parents by telephone or email. A contact mobile phone number and email address will be supplied to each subject. If skin problems develop during the study, parents will contact the study researcher.

In the same visit, a sleep video/EEG will also be performed at the INFANT sleep laboratory (Fig. 4). The timing of this should be coordinated so the recording commences following a feed around the time of the baby’s longest daytime nap. The recording will last for the duration of the baby’s sleep. A multichannel video EEG will be performed using the 10-20 system of electrode placement. Electrooculography, electrocardiography, respiration monitoring, and electromyography will be recorded simultaneously. The following parameters will be measured: duration of rapid eye movement (REM) and non-REM sleep stages, REM onset latency, sleep spindle number, density, frequency, duration, and spectral power. A quantitative analysis of the sleep EEG will be performed using multiple features of amplitude, spectral shape, continuity, and inter-hemispheric connectivity using the NEURAL software [52].

**Fig. 4 Fig4:**
[figure not shown]
Sleep pants with belt to attach sensor device for overnight actigraphy

Each parent will be provided with a pair of sleep actigraphy pants with an embedded sensor belt to monitor overnight sleep movements every night for five nights following the visit (Fig. 4).

Parents/guardians will be asked to complete monthly sleep diaries and questionnaires at seven and 8 months to collect data on the infant’s 24-hour routine, focusing on naps and sleep routine, sleep environment (crib or parent’s room), sleep position (prone or supine), and need for sleep aids (e.g. soother, rocking, patting).

At 9 months, weight, length, and head circumference will be measured again. Parents will again be asked about specific sleep problems by thorough history of the infant’s 24-hour routine, focusing on naps and sleep routine, sleep environment (crib or parent’s room), sleep position (prone or supine), and need for sleep aids (e.g. soother, rocking, patting). Parents will be asked to repeat the Pittsburgh Sleep Quality Index to reassess their own sleep. For cases, the severity of AD and symptoms of AD will be reassessed. Infant and parental quality of life will be reassessed. Treatment for AD will be amended, according to clinical response. Parental usage of products will be recorded.

Parents/guardians will be asked to complete monthly sleep diaries and questionnaires at 10 and 11 months to collect data on the infant’s 24-hour routine, focusing on naps and sleep routine, sleep environment (crib or parent’s room), sleep position (prone or supine), and need for sleep aids (e.g. soother, rocking, patting).

At 12 months, weight, length, and head circumference will be measured again. Parents will again be asked about specific sleep problems by thorough history of the infant’s 24-hour routine, focusing on naps and sleep routine, sleep environment (crib or parent’s room), sleep position (prone or supine), and need for sleep aids (e.g. soother, rocking, patting). Parents will be asked to repeat the Pittsburgh Sleep Quality Index to reassess their own sleep. Transepidermal water loss and natural moisturizing factor assessment will be repeated. Tape stripping for inflammatory cytokine analysis will be repeated. The severity of AD and symptoms of AD will be reassessed. Infant and parental quality of life will be reassessed. Treatment for AD will be amended, according to clinical response. Parental usage of products will be recorded. Each parent will be provided with a pair of sleep actigraphy pants with an embedded sensor belt to monitor overnight sleep movements every night for five nights following the visit.

At 18 months, subjects will be brought back to the INFANT Research Centre for their final study visit. At this visit weight, height, and head circumference will be measured. Mothers will be asked to fill out the Beck Depression Inventory. For cases, AD status and severity will be reassessed. In addition, a neurodevelopmental screening protocol will be completed to screen for behavioural difficulties and to ensure that all the participants are normally developing. This assessment will be performed using the CogniTOT touchscreen app (Liltoda, Cork, Ireland). CogniTOT is a touchscreen-based 10- to 15-minute cognitive assessment designed to screen for cognitive delay in young children aged 18-30 months with good concurrent validity with the Bayley’s Scales of Infant Development [53]. It will be suitable to use even if current social restrictions continue. Behaviour will be assessed using parental questionnaires. The Achenbach Child Behaviour Checklist 1 ½ - 5 is a widely-used questionnaire to assess behavioural and emotional difficulties, filled out by parents. It assesses internalizing (i.e., anxious, depressive, and over-controlled) and externalizing (i.e., aggressive, hyperactive, noncompliant, and under-controlled) behaviours. Several sub-areas are also measured, including anxiety and depression, and ‘Sleep Problems syndrome’. The Modified Checklist for Autism in Toddlers, Revised is a screening questionnaire for autism spectrum disorder. Any worrying or incidental findings will be referred for follow up along the relevant clinical pathway.

The primary outcome will be altered macrostructure of sleep at 12 months (sleep diary and actigraphy), measured as decreased sleep efficiency and increased night time awakenings. The secondary outcomes will be altered microstructure of sleep at six-eight months, measured as sleep spindle power and power in REM and NREM sleep stages; and parental sleep quality and quality of life. Outcomes will be correlated with severity of AD and inflammatory cytokines at six-eight and 12 months. In terms of safety outcomes, the clinical, neurophysiological and cytokine analyses are all safe and well-tolerated procedures with no significant associated risks. Potential confounding factors which will be controlled for in the data analysis will include parental educational level, parental depression, feeding practice, and number of siblings.

To calculate the sample size, an incidence of sleep disturbance of 60% in the infants with moderate to severe AD [17] and an incidence of 25% in healthy controls [54] will be assumed. Therefore, aiming for a power of 80% and a significance level of 5%, a total sample size of 30 subjects will be required for each group to power the dichotomous primary outcome of disturbed macrostructure of sleep and secondary outcome of disturbed microstructure of sleep. Assuming a worst-case attrition rate of 60%, and to ensure that data are available at all time points, 50 subjects will be required for each group, with a total number of participants of 100.

For descriptive statistics, mean ± standard deviation will be used, median and interquartile range for quantitative variables, and percentage with number for categories. Spearman (parametric) or Pearson (non-parametric) correlations will be applied to determine the association between dependent and independent (parental and infantile) variables. Independent variables will be fitted to logistic and linear regression models to evaluate interactions as well as to identify confounding factors. All the analyses will be carried out with the statistical software Stata, considering a *p* < 0.05 as cut-off for statistical significance. For sleep diaries, mean questionnaire scores and subsections will be compared between groups. For actigraphy, total number of overnight movements will be compared between groups. For EEG, the number, power, and density of sleep spindles, and sleep staging will be compared between groups. For parental sleep, mean questionnaire scores will be compared between groups, and qualitative parental interviews will be performed with a selection of parents of infants with AD. Qualitative data will be processed using NVIVO software.

Data will be recorded using the Castor Electronic Data Capture tool. Data will be stored on secure UCC servers. The screening and consent will take place within the first six-eight months of life at the recruiting site. Demographic details will be captured at six-eight months. Data on sleep quality will be obtained by EEG assessment during an afternoon nap at six-eight months and from overnight actigraphy recordings at six-eight months and 12 months. Data on sleep quantity will be obtained using parental sleep diaries and questionnaires from six to 12 months. Neurodevelopmental assessment will be performed at 18 months. Transepidermal water loss, natural moisturizing factor levels and skin cytokine analysis at six-eight months and 12 months will be recorded digitally. For cases, treatment logs will be kept in paper format to facilitate adjustments in treatment plans. Parents will be provided with a phone number and email address for the study to ensure easy access to the study team. Data will be entered directly onto the database by the study researcher. All data will be treated confidentially and held on a secure UCC server with restricted and password-protected access.

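### The stated diary and actigraphy comparisons yield neither primary measure (sleep efficiency, night-time awakenings), and the described diary content is not shown to supply what those measures need

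*Protocol article*

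**What the plan says.** All places are in the protocol article.

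- **Outcome (Methods/design, outcomes paragraph).** The primary outcome is "altered macrostructure of sleep at 12 months (sleep diary and actigraphy), measured as decreased sleep efficiency and increased night time awakenings". Diary and actigraphy are named together, with no statement of which source supplies which measure.
- **Analysis (Methods/design, statistical paragraph).** "For sleep diaries, mean questionnaire scores and subsections will be compared between groups". For actigraphy, the groups are compared on the total count of movements overnight. Neither sleep efficiency nor awakenings is mentioned in this paragraph.
- **Diary content (Methods/design, monthly diary paragraphs).** The diaries and questionnaires cover the infant's "24-hour routine, focusing on naps and sleep routine, sleep environment", sleep position and sleep aids.
- **Diary timing (same section).** The text schedules "monthly sleep diaries and questionnaires at seven and 8 months" and "monthly sleep diaries and questionnaires at 10 and 11 months". At 12 months it describes a history taken at the visit: "Parents will again be asked about specific sleep problems by thorough history".
- **Actigraphy (same section).** A sensor in the sleep pants records movement for five nights after the 12-month visit.
- **Data paragraph (Methods/design).** "Data on sleep quantity will be obtained using parental sleep diaries and questionnaires from six to 12 months". Sleep quality is assigned to EEG and actigraphy. The Abstract likewise says that the monthly questionnaires capture quantitative sleep.

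**The concern.** The outcomes paragraph and the analysis paragraph describe different variables. The primary outcome is two specific quantities. The stated analyses are a mean score from one source and a movement total from the other. Followed as written, the plan produces group comparisons without an estimate of the outcome that the study is meant to test, and leaves the analyst to choose the derivation after the data are in.

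The second part concerns capture. Sleep efficiency needs a period in bed as its denominator, and a count of awakenings needs a record of each waking or a rule that scores it from movement. The article describes what the diaries ask about in some detail, down to position and soothers, but does not mention these items. If they are in fact not recorded on the relevant nights, they cannot be recovered at analysis. Actigraphic efficiency would then need an assumed period in bed.

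**Working it through.** **1. What each primary measure needs.** The article defines neither, so I assume the usual meanings:

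- sleep efficiency = 100 × (time asleep) / (time in bed)
- night-time awakenings = number of wakings between sleep onset and final rising

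The first needs clock times for going to bed and rising, plus a sleep/wake record. The second needs wakings to be logged or scored.

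**2. What the stated analyses produce.**

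| Source named for the primary outcome | Comparison in the analysis paragraph | Is it sleep efficiency? | Is it a number of awakenings? |
|---|---|---|---|
| Sleep diary | Mean questionnaire scores and subsections | No | No |
| Actigraphy | Total movements overnight | No | No |

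A movement total has no time-in-bed denominator. It can rise simply because the recording is longer, and it does not separate movement during sleep from movement while awake. Two infants with the same total can therefore differ in efficiency and in number of awakenings. A mean score is a scale value, and the article gives no rule that converts it into either measure.

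**3. What the described diary content covers.**

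| Needed | Named in the diary description? |
|---|---|
| Bedtime and rising time | Not named; could fall under the 24-hour or sleep routine |
| Sleep onset | Not named; could fall under the same items |
| Number of awakenings | Not named |
| Duration of sleep | Not named there, but the data paragraph assigns sleep quantity to the diaries |

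Even if duration is recorded, it supplies only the numerator of efficiency and does not give the number of awakenings. No sentence in the article links a diary item to either primary measure.

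**4. Timing.** The named diary months are 7, 8, 10 and 11, while the primary time point and the second set of actigraphy nights are at 12 months. The data paragraph speaks of diaries and questionnaires from six to 12 months, so a 12-month diary may be intended. The article does not say that parents log times on the five actigraphy nights.

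**5. The plan's own figure, for background.** The sample size paragraph gives 30 per group for a yes/no outcome at 60% against 25%, with 80% power and a 5% level. I assume a two-sided test with pooled variance and no continuity correction. With p̄ = (0.60 + 0.25)/2 = 0.425:

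n = [1.960 × √(2 × 0.425 × 0.575) + 0.842 × √(0.60 × 0.40 + 0.25 × 0.75)]² / 0.35²

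= [1.960 × 0.699 + 0.842 × 0.654]² / 0.1225 = 30.1, rounded up to 31.

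Power at 30 per group is 79.9%, so the stated 30 stands to within rounding. Nothing in this point depends on it.

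**The case against.** The strongest reply is that the article is a condensed account. Diary items and form fields are commonly left to the full protocol. The wording gives a focus within a 24-hour routine, not a closed list. Sleep routine may include bed and rise times. Parents are also asked about specific sleep problems, and night waking fits that description. The data paragraph and the Abstract both say that sleep quantity is captured, and the outcomes paragraph itself names the diary as a source, which shows an intention to collect what is needed. Diary and actigraphy may also be complementary, with the diary giving the period in bed and the sensor giving movement within it.

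Most of this stands, and it rules out three stronger readings that a reader might infer:

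- **That neither measure can be derived from the diary at any age.** This is an argument from silence. Items that are not named are not thereby shown to be absent.
- **That half of the primary outcome is lost.** The article gives no split between diary and actigraphy, so there is no half to lose.
- **That power falls by some stated amount.** The article gives no night length, timing error or between-infant spread of sleep efficiency. Any such figure would be built on outside assumptions. A large loss would also require the timing error to be the same on every night for a given infant; errors that vary between nights would partly average out over the five nights.

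The reply does not answer the mismatch between the two paragraphs. The comparisons for diary and actigraphy are stated in the text, and they are different variables from the primary measures. A subsection of a questionnaire might concern night waking, but a subsection score is not a number of awakenings, and nothing in the stated analyses corresponds to sleep efficiency.

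**Conclusion.** The point holds in two parts of different strength.

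- **Firm.** The stated analyses of both named sources omit both primary measures, and the outcomes and analysis paragraphs must be reconciled. This rests on the text alone.
- **Conditional.** The article does not show that awakenings, or the period in bed needed for sleep efficiency, are recorded for the 12-month nights. This is a request for confirmation and not a finding that the items are missing. It assumes the usual definition of sleep efficiency.

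No numerical effect on power or bias can be given from the document. The consequence is that the primary outcome would go unestimated, or would be derived by a rule chosen after data collection. The change is worth making because items not logged on the night cannot be reconstructed later. If the items already exist in the full protocol, clarifying the text closes the matter.

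**What to change.** 1. In the statistical paragraph of Methods/design, replace the diary and actigraphy comparisons for the primary outcome with a between-group comparison of sleep efficiency and of the number of night-time awakenings at 12 months. State which source supplies each component. Mean scores and movement totals can stay as descriptive comparisons.
2. Confirm that parents record bedtime, sleep onset, each awakening and rising time on the five actigraphy nights after the 12-month visit. If they do not, add a short log to the existing email or app survey.

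Cost: an edit to the analysis paragraph and, if the log is new, about two minutes of parent time per night, or about 5 × 2 = 10 minutes per family.

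### The listed group comparisons name neither the primary measures (sleep efficiency, awakenings) nor the dichotomous outcome used for sizing, so the stated 80% power belongs to a test that is not among them

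*Protocol article*

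**What the plan says.** All the statements are in the Methods/design section of the protocol article.

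- **Definition (outcomes paragraph).** The primary outcome is "altered macrostructure of sleep at 12 months (sleep diary and actigraphy), measured as decreased sleep efficiency and increased night time awakenings". That is two quantities from two instruments.
- **Sizing (sample-size paragraph).** The plan assumes "an incidence of sleep disturbance of 60% in the infants with moderate to severe AD" and "an incidence of 25% in healthy controls". With 80% power and a 5% significance level it arrives at 30 per group "to power the dichotomous primary outcome of disturbed macrostructure of sleep and secondary outcome of disturbed microstructure of sleep".
- **Analysis (the paragraph after the sample size).** "For actigraphy, total number of overnight movements will be compared between groups". "For sleep diaries, mean questionnaire scores and subsections will be compared between groups". Logistic and linear regression are also mentioned, to examine interactions and find confounders, but no outcome is named for them. A p-value below 0.05 is the criterion throughout.

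**The concern.** The definition, the sizing and the analysis each describe a different thing. A power statement is a property of one test on one variable. Here it was worked out for a difference in proportions, while the tests listed for the same instruments compare averages and counts. An analyst could not follow both the outcomes paragraph and the analysis paragraph: for actigraphy, the first points to sleep efficiency and awakenings and the second to movement totals.

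There are two consequences. The reader cannot tell what chance the study has of detecting a difference on the comparison that will be reported. And the choice of which result counts as primary stays open until the data have been seen.

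A secondary matter is that a movement total has no denominator. The article plans five nights of recording at each of two ages. A sum over the recording depends on how many hours and nights were captured as well as on how restless the infant was.

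**Working it through.** **1. Reproduce the plan's figure.** Inputs from the sample-size paragraph: p1 = 0.60, p2 = 0.25, power 80%, alpha 5%. The article does not say whether alpha is two-sided; two-sided is assumed here. Mean proportion = (0.60 + 0.25)/2 = 0.425.

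Pooled two-proportion formula, per group:

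n = [1.960 × √(2 × 0.425 × 0.575) + 0.842 × √(0.60 × 0.40 + 0.25 × 0.75)]² / 0.35²

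= [1.960 × 0.6991 + 0.842 × 0.6538]² / 0.1225 = 30.1, rounded up to 31.

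The arcsine formula gives 29.9, so 30. Power at exactly 30 per group:

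Φ[(0.35 × √30 − 1.960 × 0.6991) / 0.6538] = Φ(0.836) = 79.9%.

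The stated 30 is therefore sound arithmetic for a comparison of two proportions.

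**2. Look for that comparison in the analysis paragraph.**

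| Item | Outcomes paragraph | Sample-size paragraph | Listed group comparison |
|---|---|---|---|
| Actigraphy | Sleep efficiency, awakenings | Disturbed, yes/no (instrument not named) | Movement total |
| Diary | Sleep efficiency, awakenings | Disturbed, yes/no (instrument not named) | Average scores and subsections |
| Scale | Two quantities | One proportion | Count or mean |

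The last column names neither the measures in the first nor the proportion in the second.

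**3. Ask what 30 per group gives for a comparison of means.** The article states no mean difference and no SD for any sleep measure, so the standardised difference d has to be assumed. For an unadjusted two-sided two-sample t-test at 5%:

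| Assumed d | Power, 30 per group |
|---|---|
| 0.3 | 21% |
| 0.5 | 48% |
| 0.8 | 86% |

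The d detectable with 80% power is 0.74 at 30 per group. As a check, the normal approximation (1.960 + 0.842) × √(2/30) gives 0.72, slightly lower because it ignores estimation of the SD.

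**4. Effect of the stated attrition.** The sample-size paragraph recruits 50 per group and allows for a worst case of 60% lost. That leaves 50 × (1 − 0.60) = 20 per group, not 30. At 20 per group the detectable d with 80% power is 0.91 (normal approximation (1.960 + 0.842) × √(2/20) = 0.89).

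**5. Movement totals.** Total = movements per hour × hours recorded. The groups' totals reflect restlessness alone only if recorded time is alike in both. The article gives no expected recording time by group, so no bias can be computed.

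**The case against.** The strongest reply is that the definition and the sizing need not conflict. Reduced efficiency and more frequent awakenings can be read as the two features of one disturbed state, which is then yes or no. On that reading only the cut-off is missing, and a cut-off, the deciding instrument and a multiplicity rule are details that a condensed article may leave to an analysis plan. Logistic regression is mentioned and would suit such an outcome, and the diary subsections might include awakenings.

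Much of this stands. The absence of a cut-off is not in itself a fault of this article. But the article does not stay silent on analysis: it lists what will be compared for each instrument, and the list does not contain the outcome that was sized. The regression models are given another purpose and no outcome, so they do not close the gap.

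A reader might infer several stronger things that the documents do not support:

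- **The primary outcome is never tested.** This is too strong, because logistic regression or a diary subsection could reach it. What can be said is that no listed group comparison names it.
- **Movement totals hide or reverse the effect.** That would require infants with atopic dermatitis to be recorded for less time. Nothing says so. Sleeping less is not the same as being recorded less, and wakefulness with the sensor on would be expected to add movements.
- **A specific false-positive rate, or a specific loss of power from requiring both measures.** Either figure needs independent tests or a decision rule that the article does not state.
- **A standardised effect read from 60% against 25%.** The conversion needs a normal variable with equal variances in both groups, cut at a single point. The plan assumes no such thing.

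The study's stated aim is descriptive, which lowers the stakes somewhat. But the article itself claims power for a named primary outcome, and that claim should attach to a planned comparison.

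**Conclusion.** The point holds as an inconsistency within the article. The primary outcome is sleep efficiency and awakenings at 12 months, the sizing is for a dichotomous outcome, and the listed group comparisons are movement totals and average diary scores. The 80% power is correctly calculated (79.9% at 30 per group, assuming a two-sided test) but belongs to a two-proportion comparison that is not listed.

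Power for the listed comparisons cannot be obtained from the article. Under assumed standardised differences of 0.3 to 0.8 it runs from 21% to 86% at 30 per group, for an unadjusted t-test. These values illustrate the range and are not estimates for this study. Dependence of movement totals on recording time is a reason to prefer a rate, but it is not evidence of bias in a known direction.

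**What to change.** Name one primary variable and make the analysis paragraph list the comparison that tests it. Either of two routes restores coherence.

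1. **Continuous (preferred).** Take actigraphic sleep efficiency at 12 months as the primary variable. Compare groups with adjustment for the confounders already listed (parental education, parental depression, feeding practice, number of siblings). Test awakenings second and treat diary measures as supportive. Report movements per recorded hour instead of totals. Restate the power: for an unadjusted t-test, 80% power needs a difference of 0.74 SD with 30 evaluable per group, or 0.91 SD with the 20 left if 60% of 50 are lost. State which evaluable number is intended.
2. **Dichotomous.** Keep the 60% against 25% calculation, define how efficiency and awakenings make an infant disturbed, and list the two-proportion or logistic group comparison as the primary test.

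A mixed model of the nightly values would also serve under the first route, but it is one option among several, and the detectable differences above are not calculated for it.

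The cost is a change of wording in the protocol and analysis plan, to be made before the data are analysed. No new data are needed. The downside is that measures not named first fall outside the main claim.

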**Methods:**

This observational study will recruit six- to eight-month old infants with moderate to severe AD and age-matched control infants who do not have AD. At six-eight months diurnal sleep electroencephalography and polysomnography will be performed in our research center. Nocturnal sleep actigraphy will be performed at home for five consecutive nights at six-eight months and 12 months. Between six and 12 months, monthly questionnaires will capture data on quantitative sleep and parental sleep. Skin barrier and immune profiles will be captured at six-eight and 12 months. AD will be assessed using standardized severity assessment tools and treated according to protocol. A neurodevelopmental assessment will be performed at 18 months to assess cognition and behaviour. An estimated sample size of 50 participants in each group is required to power the primary outcome of disturbed macrostructure of sleep and secondary outcomes of disturbed microstructure of sleep, and disturbed parental sleep, assuming an attrition rate of 60%. Potential confounding factors which will be controlled for in the data analysis will include parental educational level, parental depression, feeding practice, and number of siblings.

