Most (50-60%) children with AD report sleep disturbance [16, 17]. Sleep disturbance is a significant burden in AD and a key indicator of severity [18, 19]. AD has been demonstrated to have a negative impact on both sleep duration and quality of sleep [20–22]. Sleeplessness is also a major factor leading to impaired quality of life [7, 23]. The mechanism of sleep disturbance in patients with AD is complex and pruritus is not the sole cause [24]. Alterations in circadian rhythm, immune dysregulation and increased transepidermal water loss (TEWL) are also thought to play a role [25, 26]. Children with AD have disrupted sleep even when the dermatitis has been treated [27]. AD not only impacts on the sleep of patients but has also been shown to have a negative impact in caregivers [28]. Caregivers of patients with AD often report poorer quality of sleep, increased symptoms of insomnia and chronic sleep deprivation [29]. Co-sleeping is reported by 30% of families with a child with AD due to poor sleep [17].

Data on sleep disturbance in the first year of life in AD are extremely limited. No high-quality research using neurophysiological assessment of sleep disturbance has been performed in infants with AD under 12 months [30, 31]. In addition, very little research has been performed in sleep in infants or children under 3 years with AD. Sleep disruption in AD has generally been measured with actigraphy (measurement of movement) or caregiver-reported measures. However, polysomnography which uses electroencephalography (EEG) and other physiological signals is considered the gold standard of assessment of sleep quality [32]. Video EEG in addition to polysomnography has never been used to provide a detailed assessment of sleep quality in infants with AD.

In the ENRICH study (www.enrichstudy.com) we have recently shown the importance of EEG analysis of sleep, particularly features of sleep microstructure e.g. sleep spindles. We found that healthy infants at 4 months who had participated in a regular daily massage routine had higher power in their sleep spindles than control infants (paper submitted for publication) (Fig. 1). Sleep spindles are associated with cortical plasticity and memory consolidation and are a marker of brain maturation. In older children, increased power has been shown to be positively correlated with processing speed and cognitive ability [33, 34].

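### One sample-size calculation, based on infant sleep-disturbance rates of 60% v 25%, is said also to power EEG microstructure and, in the Abstract, parental sleep; the article gives no support for that power

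*Protocol article*

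**What the plan says.** The sample-size paragraph (Methods/design) has two rate inputs: "an incidence of sleep disturbance of 60% in the infants with moderate to severe AD" and "an incidence of 25% in healthy controls". It continues "aiming for a power of 80% and a significance level of 5" per cent, and concludes that "a total sample size of 30 subjects will be required for each group". The purpose given for those 30 is "to power the dichotomous primary outcome of disturbed macrostructure of sleep and secondary outcome of disturbed microstructure of sleep".

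The Abstract (Methods) lists more powered outcomes. After the primary outcome it names "secondary outcomes of disturbed microstructure of sleep, and disturbed parental sleep, assuming an attrition rate of 60" per cent. Parental sleep is thus powered in the Abstract but is not named in the sample-size paragraph.

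The outcomes paragraph of Methods/design defines the EEG secondary outcome as "altered microstructure of sleep at six-eight months, measured as sleep spindle power and power in REM and NREM sleep stages". It also lists parental sleep quality and quality of life, without naming a visit. The analysis paragraph compares spindle number, power and density and sleep staging between groups, and compares mean questionnaire scores for parental sleep.

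On prior EEG evidence, the Background says "No high-quality research using neurophysiological assessment of sleep disturbance has been performed in infants with AD under 12 months". The Discussion goes further and states that sleep-related EEG changes have not been studied in AD at all.

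**The concern.** A power statement belongs to a particular outcome, effect and analysis. Here one calculation, for a binary infant outcome, is extended to two others that differ from it.

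- **EEG microstructure.** The Background cites the source of the 60% for disturbance that children with AD report. Spindle power and REM/NREM power are a different construct on a quantitative scale. By the article's own account there was no EEG study in AD from which a rate could have come.
- **Parental sleep.** The rates describe infants. The outcome is a score in parents, compared by means, and no difference or SD is assumed.

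A reader told that these comparisons have 80% power could take a null EEG or parental-sleep result as evidence against an effect of useful size. The article does not say what size of effect the study could detect on those outcomes.

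**Working it through.** **Inputs from the article.** Rates 0.60 and 0.25; power 0.80; significance level 0.05; 30 per group evaluable; 50 per group enrolled; stated attrition 60%. Sidedness is not given, and two-sided is assumed. No effect size or SD is given for any secondary outcome, so standardised differences are shown over an assumed range of 0.3 to 0.8 SD.

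**Step 1: reproduce the 30.** Two proportions, 1:1, pooled variance, mean rate (0.60 + 0.25)/2 = 0.425:

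n = [1.960 × √(2 × 0.425 × 0.575) + 0.842 × √(0.60 × 0.40 + 0.25 × 0.75)]² / 0.35² = (1.370 + 0.550)² / 0.1225 ≈ 30.1, so 31 per group.

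The arcsine formula, with h = 2·asin√0.60 − 2·asin√0.25 = 0.725, gives 2 × (2.802/0.725)² ≈ 29.9, so 30. Power with 30 per group is 79.9%. The plan's figure is sound for one binary outcome at these rates.

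**Step 2: what these numbers mean for a quantity.** In SD units, the difference detectable at 80% power is d = (1.960 + 0.842) × √(2/n). The t-test figures below are slightly larger because the SD is estimated.

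| Evaluable per group | Where the number comes from | d, normal formula | d, t test |
|---|---|---|---|
| 50 | everyone enrolled has a usable first-visit EEG | 0.56 | 0.57 |
| 30 | the stated requirement | 0.72 | 0.74 |
| 20 | 50 × (1 − 0.60) | 0.89 | 0.91 |

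**Step 3: power over the assumed range (t test, two-sided 5%).**

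| True difference | 20 per group | 30 per group | 50 per group |
|---|---|---|---|
| 0.3 SD | 15% | 21% | 32% |
| 0.5 SD | 34% | 48% | 70% |
| 0.8 SD | 69% | 86% | 98% |

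**Step 4: if microstructure were dichotomised.** The 80% would still depend on EEG rates that the article does not give. With 30 per group, 50% v 25% has 52% power and 40% v 25% has 23%. These rates are illustrative.

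**Step 5: which number applies to which outcome.** The EEG is recorded at the first visit, so later loss to follow-up does not reduce it, but unusable recordings would. The Pittsburgh index is collected at the first visit, 9 months and 12 months. With no visit fixed for parental sleep as an outcome, its evaluable number cannot be read from the article.

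**The case against.** The strongest reply has three parts.

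First, the word dichotomous may be meant to cover microstructure too, with a threshold defined in a full protocol that is not shown. That is possible, and the article does not exclude dichotomisation. It does not rescue the claim, because the article gives no EEG rate, and its own definition and analysis text treat the EEG measures as quantities.

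Second, the power may in fact be enough. If the groups differed on the EEG measure by as much as 60% v 25% implies on an underlying normal scale (0.253 + 0.674 = 0.93 SD), 30 per group would give about 95% power. This stands as a limit on the point. It requires carrying the effect on reported disturbance over to the EEG, which the article neither states nor justifies.

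Third, the study is descriptive, its size rests on the binary calculation, and secondary power is often left to an analysis plan. All true, but the article does not leave it out. It asserts the power, in the Abstract and again in the Methods.

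Several stronger readings are tempting and are not supported:

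- A reader might infer that the secondary comparisons are underpowered. With no effect size given, that cannot be shown.
- A reader might infer from the Background that no EEG data exist. That sentence speaks only of high-quality research in infants under 12 months; the broader statement is in the Discussion.
- A reader might put a figure on false-positive risk by counting the EEG parameters to be recorded. That list matches neither the outcome definition nor the list of planned comparisons, and the measures are unlikely to be independent.
- A reader might conclude that one EEG variable must be ranked first. That is a preference, not something the article gets wrong.

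**Conclusion.** The point holds as a statement about support. The 60% v 25% calculation gives about 80% power with 30 per group for one binary infant outcome. The article gives no basis for claiming the same for EEG microstructure or parental sleep, and its Abstract and sample-size paragraph disagree on whether parental sleep is covered.

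In size, 30 per group reaches 80% power on a continuous outcome only for differences of about 0.74 SD or more. At 0.5 SD the power is 48%. The detectable difference runs from 0.57 SD (all 50 evaluable) to 0.91 SD (20 evaluable). These figures assume a two-sided 5% test, equal groups, an unadjusted t test and one outcome at a time. The 0.57 SD figure is a best case, since it allows for no failed recordings.

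Nothing here shows that the planned number is wrong for the binary outcome before attrition, or that a large EEG or parental effect would be missed.

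**What to change.** In both the Abstract and the sample-size paragraph, restrict the 80% power statement to the binary sleep-disturbance outcome. Make the two agree on parental sleep.

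For the secondary outcomes, replace the power claim with the standardised difference detectable at 80% power (two-sided 5%), stating the evaluable number and the visit each time:

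- EEG microstructure, first visit: about 0.57 SD if all 50 per group have usable recordings, and 0.74 SD if 30 do.
- Parental sleep, at a named visit: about 0.74 SD with 30 per group, and 0.91 SD with the 20 per group left by 60% attrition.

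The 30 should not be quoted for parental sleep as though it followed from the stated attrition, because 60% loss from 50 leaves 20.

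The cost is wording only. This point changes neither the enrolled number nor the primary analysis nor the order of outcomes. The downside is that a printed claim becomes less favourable.
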